### Moderator analyses

In additional analyses for Aims 1 and 2, we will examine age, race/ethnicity and sexual minority status as possible moderators of the intervention effect on the main outcomes of safety behaviors and IPV. Included in these models will be a group (intervention vs. control) by moderator interaction term at the second level of the model as a predictor of the slope for time. This will allow us to test if the effect of the intervention varies by the level of the moderator.

### Dose response analyses

We will examine the relationship between the number of times or “dose” the App is used during the year and change from baseline to 12-months in the main outcomes of safety behaviors and IPV using multiple regression. We will control for baseline scores on the outcome measures in this analysis as the level of use of the App may depend on severity of violence. This analysis will examine if repeated use of the App results in greater improvement in the outcome scores.

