
### Baseline data collection

Participants access the study website or App to complete data collection. This has several advantages: the participant can complete the instruments whenever it is convenient, and the data are entered by the participant, eliminating at least two sources of error – misreading hand-written forms and data input error. Electronic data collection may reduce social desirability bias compared to face-to-face interviews [38, 39]. For ease and to keep participants engaged with the website and App, we use radio buttons (i.e., on-screen buttons that allow selection from a group of options) and clickable sliding bars to answer questions. Participants can contact the RA if they have technical problems with the website or App, questions or concerns about the study, or need help finding someone safe to talk to. If participants contact the RA for assistance with safety or distress, the RA will be trained to respond with compassion and will provide the participant with the National Dating Violence Hotline phone number and website. Participants who do not complete the baseline assessment within the first four days will be sent an automated reminder email. The RA will determine if the participants received the email/password, had any problems accessing the App, or had any follow-up questions. The RA will continue to follow-up with participants who have consented and have not completed the session using the safe contact information provided by the participant until: 1) the sessions are completed, 2) the participant indicates they have decided not to continue with the study, or 3) 6 weeks from the date of enrollment has passed. If the App session is not completed within following the 4 day auto-reminder email, the RA sends manual reminders via email (3 attempts) then text/phone (up to 5 attempts, up to 3 messages left) using safe contact information provided by the participant. The baseline window closes and attempts to contact cease 6 weeks after enrollment. If at 6 weeks the participant has not logged into the App/website or completed baseline measures, they will be dropped from the study.

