
### Description of the generic IPV resource App (Control App)

The control App is based on usual safety planning services college women and friends have access to on-campus and on the Internet through IPV websites. We will not use the DA or DA-R for risk assessment in the relationship as these are specific components of the safety decision App intervention, but we will assess risk factors for severe violence as identified on IPV websites (such as the Red Flag Campaign). The control group App will provide women and friends with brief safety planning information and IPV resources targeted to college students age 18–24 years. The control group App safety plan is not personalized to women’s/friends’ safety priorities and danger in the relationship. As detailed above, we will collect information on women’s/friend’s use of the control App, including number of times the App is accessed, time spent using the App, and content accessed.

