### Follow-up sessions

Follow-up App sessions for both groups will be conducted at 6 and 12 months post-baseline. These time points are selected for several reasons, including findings from previous research that IPV frequency and severity often increases over the course of a violent relationship, making it important that participants have access to the App to input changes in risk factors for IPV and review their safety plan at multiple time points [20]. Further, follow-up contacts provide important opportunities for the RAs and study participants to reconnect related to the study and supports retention of participants that may have to relocate for safety. Participants will be encouraged by email, text and phone contact by the RA to access the password-protected App to complete the session and follow-up assessment. As noted above, for all outreach to participants, the RA will use safe contact information and preferred mode of communication provided by the participant. The post-baseline data collection will consist of the same questions collected at baseline but will focus on outcomes since the previous session. For example, participants will be asked about threatened or actual IPV since the previous session/assessment.

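### The dose-response regression counts App use over the same year as the outcome change, adjusts only for baseline scores and is worded causally, so use that follows violence can pass for an effect of use

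*Protocol article*

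**What the plan says.** The section Dose response analyses fixes four things.

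- **Exposure:** "the number of times or “dose” the App is used during the year".
- **Outcome:** "change from baseline to 12-months in the main outcomes of safety behaviors and IPV using multiple regression".
- **Adjustment:** "We will control for baseline scores on the outcome measures in this analysis". The reason given is "as the level of use of the App may depend on severity of violence".
- **Reading:** "This analysis will examine if repeated use of the App results in greater improvement in the outcome scores".

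Three other places bear on it. Follow-up sessions says that "IPV frequency and severity often increases over the course of a violent relationship", and uses this to justify giving participants App access at several time points so that changed risk can be entered. Under Outcomes, the Composite Abuse Scale asks about the last 6 months, so the 12-month score covers roughly months 6–12. Data analyses has a general covariate rule, but it concerns baseline differences between the randomised groups and would not bring violence during follow-up into this model.

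**The concern.** The plan names a confounder, severity of violence, but controls only its value at baseline. The exposure is accumulated after baseline, over the same months in which the outcome arises. If women open the App more often when violence rises, use is partly a consequence of the outcome, and no baseline covariate can undo that.

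For IPV the distortion has a predictable sign: more violence, more use, worse 12-month score. An App that does nothing would appear to harm frequent users, and one that helps could appear useless. Because the stated reading is causal, such a coefficient would be taken as evidence on whether repeated use helps abused women.

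**Working it through.** The article gives no figure for this analysis, so there is nothing to reproduce. The check asks how often the planned model declares a dose effect on IPV when none exists.

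**Inputs from the article**

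- 300 survivors (Recruitment). Equal allocation, which I assume, gives 150 per arm.
- 20 % attrition (Statistical power): 150 × 0.8 = 120.
- Correlation of 0.3 between visits (Statistical power), applied here to all pairs of visits.

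**Assumptions not in the article**

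- The regression is run in one arm.
- IPV scores b (baseline), y6 and y12 are standardised.
- Use in each half-year has variance 1 and correlates g with severity in that half-year.
- Dose is the sum over the two half-years, and its true effect is zero.
- g is unknown, so a range is shown.

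**Planned model:** y12 − b regressed on dose and b. With b in the model, the dose coefficient is the same as for y12, so the test depends on the partial correlation of dose and y12 given b.

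- Var(y12 | b) = 1 − 0.3² = 0.91
- Cov(y6, y12 | b) = 0.3 − 0.3² = 0.21
- Cov(dose, y12 | b) = g × (0.21 + 0.91) = 1.12 g
- Var(dose | b) = 2(1 − g²) + g²(2 × 0.91 + 2 × 0.21) = 2 + 0.24 g²
- Partial correlation ρ = 1.12 g / √[0.91 × (2 + 0.24 g²)]
- By Fisher's transformation, the expected z is atanh(ρ) × √(n − 4). The false-positive rate is P(|Z + z| > 1.96), with Z standard normal.

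For g = 0.2 and n = 120: ρ = 0.224 / √(0.91 × 2.0096) = 0.166, z = 0.1672 × √116 = 1.80, and the rate is 44 %.

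| g | ρ | rate, n = 120 | rate, n = 150 |
|---|---|---|---|
| 0 | 0 | 5 % | 5 % |
| 0.1 | 0.083 | 15 % | 17 % |
| 0.2 | 0.166 | 44 % | 52 % |
| 0.3 | 0.248 | 78 % | 86 % |

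Simulation of the same model (3,000 to 4,000 trials per setting) agrees. At n = 120 repeated runs gave 13–16 %, 43–45 % and 78–79 % for g = 0.1, 0.2 and 0.3. From g = 0.1 upward practically all false positives were positive, meaning more use with more IPV.

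**Sensitivity to the form of the model.** With Poisson counts of use, log-mean 1 + 0.2 × baseline + h × follow-up violence, and a correlation of 1.0 or 0.7 between follow-up violence and the 12-month score, rejection at n = 120 was 4.4–4.6 % at h = 0, 19–41 % at h = 0.1, 64–92 % at h = 0.2 and 90–100 % at h = 0.3. When use depends on baseline violence alone, the planned adjustment works.

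**Alternatives, under no App effect, n = 120 per arm**

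- Use in months 0–6 against the 12-month score, adjusted for baseline and 6-month scores: about 5 % at every g.
- Dose-by-arm term on whole-year use: about 5 % when g is equal in the two arms, about 24 % at 0.3 against 0.1, and 47–49 % at 0.3 against 0.
- Dose-by-arm term within the lagged model: about 5 % in all these cases.

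**Cost of the lagged model.** Suppose early use lowers the 6-month score by 0.3 SD and 0.6 of that carries over. The total effect at 12 months is −0.3 × 0.6 = −0.18. After adjustment for the 6-month score the estimate is about 0.00, and rejection falls from 51 % to 5 %.

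**The case against.** The strongest reply is that this is a supplementary analysis, that the authors saw the link between severity and use and adjusted for it, and that nothing in the article shows that use tracks violence during follow-up. Follow-up sessions speaks of having access to the App, mainly to justify the 6- and 12-month sessions. It does not tell women to log in when violence rises. This stands in part: the bias is conditional, its size rests on an assumed g, and at g = 0 there is none. It does not rescue the causal wording, because the article's own reason for adjusting applies equally to violence after baseline.

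Three stronger readings are tempting but not supported.

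- A reader might infer that the false dose effect is bound to appear. The article makes it plausible only.
- A reader might infer that safety behaviours will show a spurious benefit because active help-seekers also use the App more. The outcome is the percentage of behaviours tried that were found helpful. Trying more raises the denominator and need not raise the percentage, so the direction is open.
- Because "Participants access the study website or App to complete data collection", a reader might infer that the dose counts survey sessions. The logs also record time spent and content accessed, so these sessions may be separable. Which accesses count is a definition that an article commonly leaves to the analysis plan.

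**Conclusion.** The point holds in conditional form. With exposure and outcome sharing one window and only baseline scores controlled, the planned regression cannot tell an effect of use from use driven by violence during follow-up. For IPV the error runs toward apparent harm or a masked benefit. The false-positive rate is about 15 % to 78 % at n = 120 for g between 0.1 and 0.3, against a nominal 5 %.

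These figures illustrate a mechanism and do not forecast the trial's result. They rest on the assumed g, one arm with 20 % attrition, a correlation of 0.3 between visits and a continuous IPV score. They do not extend to the percent-helpful outcome. The randomised comparison under Intervention effectiveness is untouched, and no design or sample-size decision depends on this analysis. It should still be corrected, because the stated causal reading could mislead about repeated use.

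**What to change.** In Dose response analyses:

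1. Word the aim and the result as an association: whether repeated use *is associated with* greater improvement. This is needed whichever model is fitted, because unmeasured help-seeking remains.
2. Add a lagged analysis: App use in months 0–6 against the 12-month outcome, adjusted for baseline and 6-month scores. State its downside with it: it ignores use after month 6 and removes any early effect of use that acts through the 6-month score, so a null result does not show that use had no effect.
3. A dose-by-arm comparison may be added to the lagged model as supportive only. The data exist, since the trial will log "use of the control App, including number of times the App is accessed". It cancels a common propensity to use only if use responds to violence similarly in both arms. That is uncertain, because the control App is not personalised and omits the Danger Assessment.

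The cost is wording and analysis time. The use logs and the 6-month assessment are already planned, so no new data are needed. The interaction term will be less precise than a slope within one arm.

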### Statistical power

We based the power analysis on a repeated measures ANOVA, but propose to use multilevel modeling for the analyses which allows all cases with missing data to be included in the analyses. We do not have adequate estimates of the within and between variance to estimate power for the multilevel model directly. However, in general multilevel model approaches are more powerful than repeated measures ANOVA. We have powered the study at the .90 level rather than .80 as we want to have adequate sample sizes to conduct exploratory analyses of the moderators of the intervention effect if necessary. Since the primary purpose of the safety intervention is to increase safety-seeking behaviors, the power analysis is based on an effect size calculated from the results from a previous IPV intervention [36]. These investigators evaluated the effect on safety-seeking behaviors of a telephone intervention compared to usual safety services in Spanish-speaking and English-speaking women who obtained restraining orders. The effect size, f, was computed to be 0.58, and according to Cohen’s conventions, this represents a medium effect size. Using means obtained from the telephone intervention study, this effect size is equivalent to a mean change from baseline to follow-up of 14.4 % for the intervention group compared to a change of 10.4 % in the control group from baseline to 12-months. Assuming an autocorrelation of 0.3, 300 participants in the intervention and 300 participants in the usual safety services group provide 0.99 power to detect a significant group by time interaction at the 0.05 alpha level. Assuming an attrition rate of 20 % and the same parameters as above, the study will have 0.99 power to detect a significant effect of the intervention. Even in a scenario where the attrition rate would be 37.5 %, the study would still have adequate power greater than .90 to detect a significant group by time interaction. Our prior work in this area suggests that 20 % is a reasonable attrition rate and we have successfully used multiple strategies to reduce attrition as described above.

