## Methods

### Objectives

Our overall goal is to develop evidence-based interventions for college-aged women that prevent dating violence and limit the long-term negative physical and mental health consequences of IPV. Our objective is to evaluate the effectiveness and dissemination of an interactive, personalized smartphone application (“App”) intervention and website, named MyPlan, for: 1) college women (age 18–24) who experience IPV and 2) friends (age 18–24) of women experiencing IPV. The MyPlan safety decision App allows the user to enter information on: a) relationship health; b) safety priorities; and c) severity of violence/danger in the relationship. The MyPlan App then provides the user with a personalized safety plan with links to resources. Findings from our previous research with an internet-based safety decision aid [36] and from previous testing of the MyPlan App Prototype [37] suggest this approach offers college women and friends a unique opportunity to privately consider safety priorities, informs users about danger in the relationship, and provides an ongoing, accessible resource for safety. Therefore, our interdisciplinary team is examining two aims over 3 years:Aim 1. Test the effectiveness of MyPlan, an interactive, personalized safety decision App, on abused university/college women’s decisional conflict, safety behaviors, and IPV experience compared to women randomized to the control group (a generic IPV resource App). We hypothesize women in the MyPlan safety decision App group will have reduced decisional conflict about safety priorities which will lead to increased safety-behaviors (including reduction in alcohol/drug use) and reduced IPV at six, and 12 months post-baseline in comparison to the control group.Aim 2. Test the effectiveness of MyPlan, an interactive, personalized safety decision App, on abused university/college women’s friends’ (male and female) awareness of IPV, decisional conflict, confidence to intervene, and support provided to friends, compared to friends randomized to the control group (a generic IPV resource App). We hypothesize that friends in the MyPlan safety decision aid App group will have increased awareness of IPV and reduced decisional conflict about safety priorities, which will lead to increased supportive behaviors and confidence to intervene in comparison to the control group.

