### Outcomes

The primary outcomes for Aim 1 for survivors consist of:*Use of safety strategies*: The Safety Behavior Checklist adapted from Sullivan & Bybee [40] and Parker & colleagues [41] measures the range of strategies used by survivors to halt or escape violence. This instrument asks if each strategy has been used over the last 6 months and if the strategy was helpful in dealing with the abusive partner or abuse. The checklist includes use of formal services (e.g., Have you met/called/texted/instant messaged a professional that works on campus (e.g. a professor, campus administrator, campus staff at a women’s center or campus health clinic) about your partner hurting you (physically, sexually, or emotionally?, Did you get/try to get an order of protection (or restraining order) against your partner?) and informal safety steps (e.g., Have you developed a code/signal so others would know when you were in danger from your partner?, Have you identified a safe place on campus or in the community you could go if your partner became dangerous?). The percent of safety behaviors tried by survivor that she found helpful will be the primary outcome.*Decisional conflict immediately post intervention*: The decision process for survivors is measured with questions adapted from validated subscales of the Decisional Conflict Scale (DCS) [42, 43]. The DCS tests whether using this safety planning decision aid helps a woman to understand the advantages and disadvantages of safety planning options and to know her values related to them. The Decisional Conflict Scale discriminates between people who make decisions and those who delay making decisions. The DCS consists of twelve items (e.g., “I know the risks of taking steps to increase my safety in my relationship”, “I am clear about which benefits of the relationship are most important to me”, “I have enough support from others to make decisions about my safety”) with a 5-point likert response scale from ‘strongly agree’ to ‘strongly disagree’. The DCS provides a total score, which is a measure of the decision process, as well as scores for four subscales (feeling informed, certainty about decision, values clarity, and support), with higher scores on the DCS indicating a greater degree of decisional conflict (indicative of a poorer decision process) [39, 40]. Decisional conflict will be measured pre and post the first use of the decision aid.

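### Statistical power: f = 0.58 is called medium but lies well above large on the f scale, and no SD is given, so the stated 0.99 cannot be relied on for a 4-point difference in the primary outcome

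*Protocol article*

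**What the plan says.** The Statistical power section takes its effect size from an earlier study: "These investigators evaluated the effect on safety-seeking behaviors of a telephone intervention compared to usual safety services", in women who had obtained restraining orders. It reports "The effect size, f, was computed to be 0.58" and adds that, by Cohen's conventions, "this represents a medium effect size". It then translates the figure: "this effect size is equivalent to a mean change from baseline to follow-up of 14.4 % for the intervention group". The corresponding change among controls, at 12 months, is put at 10.4%.

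The calculation continues: "Assuming an autocorrelation of 0.3, 300 participants in the intervention and 300 participants in the usual safety services group" give power 0.99 for the group-by-time interaction at alpha 0.05. Power is put at 0.99 with 20% attrition and above 0.90 with 37.5% attrition. No SD appears, and the section concedes that the variance components are not adequately known.

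For survivors, the Outcomes section says: "The percent of safety behaviors tried by survivor that she found helpful will be the primary outcome". The earlier study carries reference number 36, but the Objectives section uses that number for a different kind of study: "Findings from our previous research with an internet-based safety decision aid [36".

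**The concern.** With no SD given, the standardised effect carries the whole power claim, and it is described in two ways that cannot both be right. Cohen's benchmarks are 0.10, 0.25 and 0.40 for f, and 0.50 is medium for d. A value of 0.58 is far above large as f and close to medium only as d.

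The choice matters because the section also gives the effect in raw percentages. Once a standardised effect and a raw difference are both stated, the SD is fixed, and that SD can be compared with what the primary outcome could show. If the true SD is larger than the implied one, the 4-point difference has less power than claimed. A reader who relied on 0.99 would then give a null result more weight than it deserves.

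**Working it through.** **Inputs from the protocol article.** Effect 0.58; changes of 14.4% and 10.4%; autocorrelation 0.3; alpha 0.05; 300 per arm; attrition 20% and 37.5% (Statistical power). 300 survivors in total (Recruitment). **Assumptions.** An even split of survivors; the percentages lie on the scale of the primary outcome; the SDs of change named below.

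**1. The plan's own figure.** For the repeated-measures interaction, λ = f²·N·m/(1−ρ). With f = 0.58, N = 600, m = 3 and ρ = 0.3, λ = 0.3364 × 600 × 3 / 0.7 = 865, and power exceeds 0.999. It also exceeds 0.999 at N = 480 (20% attrition) and N = 375 (37.5%). The stated 0.99, 0.99 and above 0.90 therefore follow from the inputs.

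**2. The SD that the two statements imply.** Difference in change = 14.4 − 10.4 = 4.0 points. For two equal groups compared on a change score, d = 2f.
- 0.58 read as f: d = 1.16, SD of change = 4.0/1.16 = 3.4 points.
- 0.58 read as d: SD of change = 4.0/0.58 = 6.9 points.

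**3. Relabelling to d only.** Two-sample normal approximation, power = Φ(d/√(2/n) − 1.96), with d = 0.58:
- 300 per arm: above 0.999
- 150 per arm: 0.999
- 120 per arm: 0.994
- 93.75 per arm (150 less 37.5%): 0.978

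**4. Are these SDs plausible for this outcome?** The outcome is a proportion within each woman. As an illustration, let a woman try k strategies, each found helpful with probability p. Binomial scatter alone gives SD of change = 100·√(p(1−p)/k)·√(2(1−0.3)), where the last factor is 1.18.

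| k tried | p = 0.6 | p = 0.9 |
|---|---|---|
| 20 | 13.0 | 7.9 |
| 30 | 10.6 | 6.5 |

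At p = 0.6, k = 10 gives 18.3 and k = 5 gives 25.9. Solving for k at p = 0.9, k = 10000 × 0.09 × 1.4 / SD²: about 26 strategies for an SD of 6.9 and about 106 for 3.4 (unrounded SDs). At p = 0.6 the counts are about 71 and 283. True differences between women in change would add to the SD. So 3.4 is implausible, and 6.9 needs favourable conditions.

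**5. Power for the 4-point difference by assumed SD of change.** Power = Φ(4/(SD·√(2/n)) − 1.96). For SD 15 and n = 120: 4/(15 × 0.1291) − 1.96 = 0.106, power 0.54. The survivor arm is 300/2 = 150, and 150 × 0.8 = 120 after 20% attrition.

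| SD of change | 300 per arm | 150 per arm | 120 per arm |
|---|---|---|---|
| 10 | 0.998 | 0.93 | 0.87 |
| 15 | 0.90 | 0.64 | 0.54 |
| 20 | 0.69 | 0.41 | 0.34 |
| 25 | 0.50 | 0.28 | 0.24 |

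Power of 0.90 needs an SD of change of at most 15.1 points at 300 per arm, 10.7 at 150 and 9.6 at 120.

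**6. Detectable difference with 120 per arm.** (1.96 + 0.84)·√(2/120) = 0.36 SD at 0.80 power; (1.96 + 1.28)·√(2/120) = 0.42 SD at 0.90.

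**The case against.** The strongest defence is that this is a labelling slip. The stated powers reproduce, and if 0.58 is really a d they stay above 0.97 even at about 94 per arm. That stands: the arithmetic is sound given its inputs, and correcting the index alone does not overturn the conclusion.

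The argument about SDs also rests on assumptions. The article gives neither the length of the checklist, nor the number of strategies tried, nor the share found helpful. At 20 to 30 tried and 90% helpful, the illustrative SD of change is 7.9 to 6.5, so 6.9 cannot be excluded. This stands too, and it is why the result is given as a range.

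A reader might infer that f = 0.58 is absurd because the repeated-measures formula already gives power 0.998 with 20 participants in total. That should not be set beside the SD of 3.4, because the two use different definitions of f. With d = 2f on a change score, 20 participants give only 0.69. Nor is surplus power a contradiction, since the section says it wants room for moderator analyses.

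A reader might also infer that the source study measured a different outcome. The intervention and the population plainly differ, but the section does not say what its percentages measure, so neither the same outcome nor a different one is shown. The double use of reference 36 is a citation problem and does not affect power.

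Finally, the 120-per-arm column depends on survivors being analysed separately, whereas the section counts 300 per arm. That mismatch is a separate matter. The 300-per-arm column shows the present point without it.

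**Conclusion.** The point holds as a contradiction in the key planning input together with a missing SD. As f, 0.58 is not medium; as d, it is close to medium, but the text says f. With the stated 4-point difference it implies an SD of change of 3.4 points, which is implausible, or 6.9 points, which is optimistic.

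The documents do not support the stronger readings that the power claim has no basis at all, that neither SD could occur, or that 4 points could never be detected with good power. At an SD of 10, power is 0.998 with 300 per arm and 0.87 with 120.

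What they do support is that 0.99 cannot be relied on for a 4-point difference in the actual primary outcome. Over SDs of change from 10 to 25 points, power runs from 0.998 down to 0.50 at 300 per arm, and from 0.87 down to 0.24 at 120. These ranges assume that the percentages lie on the primary-outcome scale and, for the 120, an even split of survivors with 20% attrition. The SDs are assumed, not taken from the article.

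**What to change.** Rewrite the Statistical power paragraph as follows.
- State whether 0.58 is f or d, and make the verbal label agree.
- Say what the 14.4% and 10.4% are percentages of, and reconcile the two uses of reference 36 (Objectives and Statistical power) so that the source can be traced.
- Give the SD of change of the survivors' primary outcome and its source; the team's earlier decision-aid study may supply it. If none is available, tabulate power for the 4-point target over assumed SDs of 10 to 25 points, at the arm size actually randomised for survivors.
- Add the detectable difference: with 120 per arm, about 0.36 SD at 0.80 power and 0.42 SD at 0.90.

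The cost is one recalculated paragraph and a less favourable power statement. No extra participants are needed.
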